### 9.2 OUTCOME MEASURES

**Primary:**

1. All-cause mortality within the first 10 weeks (non-inferiority)

**Secondary:**

1. Early Fungicidal Activity derived from Serial LPs on days 1, 7 and 14.
2. Clinical and laboratory-defined grade III/IV adverse events; median % change from baseline in laboratory defined parameters.
3. PK parameters and PK/PD associations of single high dose L-AmB.
4. Health service costs.
5. All-cause mortality within the first 2 and 4 weeks
6. All-cause mortality within the first 10 weeks (superiority)
7. Rates of cryptococcal relapse / IRIS within the first 10 weeks
8. Disability at 10 weeks measured using a simple two question assessment and modified Rankin Score

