#### ii) Laboratory:

- Full blood count (FBC), urea, creatinine, electrolytes, alanine transaminase (ALT)
- HIV serology – if status not already known (with documentation of result)
- CD4 count, and VL if on ART as is routine at the site(s)
- Pregnancy test – urine or serum in women of reproductive age
- CSF: opening pressure, cell count and differential, protein, glucose, India ink, quantitative fungal culture, routine culture, cryptococcal antigen

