#### ii) Laboratory data:

Day 3, 5, 7, 10, 12, 14: Creatinine, Electrolytes

Day 7, 14: Full blood count, ALT

Week 4 (clinic): Full blood count, Creatinine, Electrolytes, ALT

At the time of monitoring blood tests, and at additional times (see schedule below), an extra 2.5 ml of blood will be taken for PK studies.

Days 7, 14: Follow up CSF examinations (performed by study team) for: opening pressure, quantitative fungal culture, CSF for drug levels, immune parameters.

| TABLE 6.1. Event Schedule         | Screening | Week 1 |    |    |    |    |    |    | Week 2 |    |     |     |     |     |     | Wk 4 | Wk 6 | Wk 8 | Wk 10 | Wk 16 |
|-----------------------------------|-----------|--------|----|----|----|----|----|----|--------|----|-----|-----|-----|-----|-----|------|------|------|-------|-------|
| Study Day                         | ≤D0       | D1     | D2 | D3 | D4 | D5 | D6 | D7 | D8     | D9 | D10 | D11 | D12 | D13 | D14 |      |      |      |       |       |
| Consent forms              |           |        |    |    |    |    |    |    |        |    |     |     |     |     |     |      |      |      |       |       |
| PIS and signed consent            | X         | X      |    |    |    |    |    |    |        |    |     |     |     |     |     |      |      |      |       |       |
| Follow up                  |           |        |    |    |    |    |    |    |        |    |     |     |     |     |     |      |      |      |       |       |
| Screening and randomisation       | X         | X      |    |    |    |    |    |    |        |    |     |     |     |     |     |      |      |      |       |       |
| Clinical review                   |           | X      | X  | X  | X  | X  | X  | X  | X      | X  | X   | X   | X   | X   | X   |      |      |      |       |       |
| Outpatient follow-up              |           |        |    |    |    |    |    |    |        |    |     |     |     |     |     | X    | X    | X    | X     |       |
| Week 16 telephone                 |           |        |    |    |    |    |    |    |        |    |     |     |     |     |     |      |      |      |       | X     |
| Clinical labs              |           |        |    |    |    |    |    |    |        |    |     |     |     |     |     |      |      |      |       |       |

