## 6.3 PROCEDURES FOR ASSESSING SAFETY

There is considerable experience with L-AmB doses up to 10 mg/kg/d. In a trial of treatment for filamentous fungal infections with 100 patients per arm, daily dosing at 10 mg/kg/d compared with 3 mg/kg/d, for 14 days, was associated with increased nephrotoxicity. However, rates of doubling of creatinine and of hypokalaemia were still only those seen with the use of conventional D-AmB formulation 0.7 mg/kg/d in cryptococcal meningitis. Single dose and intermittent L-AmB at up to 10 mg/kg/d has been very well tolerated. Serum creatinine and potassium will be monitored at predetermined intervals to ensure any adverse effects are recognised early and appropriate management undertaken. .

Proportions of patients in different arms suffering clinical and laboratory-defined side effects will be compared as well as the mean percent change from baseline of laboratory values in the treatment groups. Mortality by treatment group will be analysed by summary statistics and time to event analyses, unstratified and stratified for possible confounding factors. The frequency and severity of any immune reconstitution reactions, the factors associated with occurrence of reactions and the frequency of further AIDS-related illnesses will also be determined. These parameters will be reviewed during the study by the Independent Data Monitoring Committee (IDMC – see [Section 9.4](#))

Throughout the study patients will be closely monitored for signs and symptoms of drug toxicity. All toxicities leading to temporary or permanent discontinuation of the study therapy, and all Grade 3 or 4 toxicity effects will require thorough investigation with relevant clinical and laboratory tests as clinically indicated. These should be repeated until final resolution or stabilization of the toxicity. All symptoms and laboratory findings will be graded according to severity using the modified Division of AIDS toxicity criteria.

In the event that the day 7 lumbar puncture identifies an increase in colony forming units from baseline this must be reported as an SAE. The co-ordinating centre will be responsible for managing this situation on a case-by-case basis.

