#### Secondary analyses.

We will conduct further analyses of the primary endpoint and analyse the secondary endpoints. These analyses will be done using a 5% two-sided significance level (i.e. to test for superiority).

Analyses of survival data will be conducted using unadjusted Cox regression analysis to calculate the hazard ratio (HR) and 95% CI between the treatment groups. Kaplan-Meier survival curves, and

survival percentages at 2, 4 and 10 weeks, will also be calculated by treatment group and overall. A log-rank test will be done to compare the survival curves between the treatment groups.

Proportions will be analysed using GLMs with treatment group as the sole predictor. The point estimate of the treatment effect with two-sided 95% CI will be derived.

For the analyses of cryptococcal clearance rates, we will perform linear regression of  $\log_{10}$  CFU against time for each patient. The means rates of decrease in  $\log_{10}$  CFU/ml/day will be compared between the two groups. We will calculate the difference in means together with the 95% CI. Rates of CFU decline will also be modelled using General Estimating Equations (GEE) methods.

Sensitivity analyses of the primary endpoint making different assumptions for the losses to follow-up will be conducted. Covariate-adjusted analyses for the primary endpoint will be conducted by adding pre-specified covariates into the GLM model to derive the adjusted risk difference and the upper limit of one-sided 95% CI. Imputation for baseline missing covariates will be made for the covariate-adjusted analysis.

**Stratified analyses:** Analyses stratified by ART status and other pre-defined baseline variables, such as clinical stage, will be performed. The other baseline variables will be defined in the analytical plan.

A full definition and explanation of all primary, secondary and stratified statistical analyses will be included in the statistical analysis plan.

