**PK-PD analysis:** Plasma samples will be collected to describe the PK of liposomal amphotericin B, and enable the PK-PD of L-AmB for CM and the impact of PK variability on outcome to be determined. The serum PK of fluconazole will also be described. A portion of the CSF sample obtained for quantitative counts will be reserved to measure fluconazole concentrations, and thereby estimate the extent of penetration of fluconazole into the CSF. We will not attempt to measure concentrations of amphotericin B in CSF, as the drug is concentrated in the meninges and cannot be reliably detected in CSF. The PK-PD data will be modelled using a population methodology, using the program Pmetrics.

**Safety:** The safety analysis will be descriptive and the frequency and proportions of patients suffering clinical and laboratory-defined side effects (DAIDS grade III/IV adverse events) will be generated by treatment arms.

**Economic analysis:** An economic analysis will be conducted to provide evidence for the cost-effectiveness of short-course L-AmB treatment. The objective of the economic analysis is to estimate the cost consequences and the cost-effectiveness of short-course L-AmB treatment, compared to current care. Both societal and healthcare perspectives are chosen, and health service patient costs including household costs, treatment cost and hospitalisations in both arms will be compared over the trial period in a probabilistic approach, using Monte Carlo bootstrapping methods in STATA, @Risk software, and TreeAge. In the country-specific cost-consequence analyses, the societal and health service costs will be compared, and used along with the trial-wide primary endpoint data to perform cost-effectiveness modeling using a decision-tree model for each country with historical data as comparison.

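### Continuous laboratory toxicity is named only as percent change from baseline (median in one place, mean in another) with no baseline adjustment stated, and the protocol is inconsistent on whether the arms are compared on it

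*Protocol*

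**What the plan says.** **The measure.** The Summary of Trial table, the Outcome Measures list, Section 1.3 (secondary objective 2) and Section 9.2 (secondary outcome 2) all name "median % change from baseline in laboratory defined parameters", next to the proportions with grade III/IV adverse events. Section 6.3 says that the proportions with side effects "will be compared as well as the mean percent change from baseline of laboratory values in the treatment groups". No other continuous laboratory measure appears.

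**The status of the analysis.** Section 9.5 says of further analyses of the primary endpoint and of the secondary endpoints: "These analyses will be done using a 5% two-sided significance level". Its safety paragraph says: "The safety analysis will be descriptive". That paragraph goes on to mention only frequencies and proportions of side effects.

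**The data.** Section 5.1 collects full blood count, urea, creatinine, electrolytes and ALT at baseline, and Table 6.1 schedules them on day 1. Section 6.1 schedules follow-up as "Day 3, 5, 7, 10, 12, 14: Creatinine, Electrolytes" and "Day 7, 14: Full blood count, ALT", with all of these again at week 4.

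**Adjustment.** Section 9.5 plans covariate adjustment for the primary endpoint, and Section 6.2 plans adjustment of the clearance-rate analysis for baseline fungal load. Nothing similar is stated for laboratory values. Full definitions of the analyses are left to the SAP, which is not at hand.

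**The concern.** Two things are unsettled. First, the sections disagree on the summary (median or mean) and on its role (compared, tested or described), so a reader cannot tell what the laboratory result will be.

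Second, if the arms are compared on percent change as named, the comparison is weaker than the data allow. Percent change is skewed, since a halving is −50% and a doubling is +100%. It also depends on the baseline value, because a low baseline tends to give a large rise. Without adjustment, a chance imbalance in baseline creatinine or haemoglobin passes into the result, and a difference in medians adds a further loss.

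This matters because lower toxicity is part of the stated case for the short-course regimen (Sections 1.1, 1.5 and 9.3), and the laboratory values are direct evidence on it.

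**Working it through.** **No stated figure to reproduce.** The protocol gives no SD, correlation, power or sample size for laboratory change. Its sample size concerns mortality: (1.645 + 1.282)² × 2 × 0.35 × 0.65 / 0.10² = 389.8, so 390 per arm as stated. That figure is right and has no bearing on this point.

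**Assumed inputs.** Log-scale SD 0.35 at baseline and 0.40 at follow-up; correlation ρ from 0.3 to 0.8; lognormal values; 300 evaluable patients per arm; a small treatment effect.

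**Variance per patient on the log scale**
- Follow-up adjusted for baseline: A = 0.40² × (1 − ρ²).
- Unadjusted log change: C = 0.35² + 0.40² − 2ρ × 0.35 × 0.40 = 0.2825 − 0.28ρ.

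**Efficiency relative to the adjusted log model**
- Difference in median % change: (2/π) × A/C. The log of (1 + % change) is the log change, which keeps the order of values, and a sample median of normal data has π/2 times the variance of the mean.
- Difference in mean % change: A/(e^C − 1), because e^C − 1 is the squared coefficient of variation of a lognormal ratio.

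| ρ | A | C | e^C − 1 | Efficiency, medians | Loss | Efficiency, means | Loss |
|---|---|---|---|---|---|---|---|
| 0.3 | 0.1456 | 0.1985 | 0.2196 | 0.47 | 53% | 0.66 | 34% |
| 0.5 | 0.1200 | 0.1425 | 0.1532 | 0.54 | 46% | 0.78 | 22% |
| 0.7 | 0.0816 | 0.0865 | 0.0904 | 0.60 | 40% | 0.90 | 10% |
| 0.8 | 0.0576 | 0.0585 | 0.0602 | 0.63 | 37% | 0.96 | 4% |

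Simulations of this setting give about the same: losses of 34–53% and 38–51% for medians, and 5–29% and 4–34% for means. In patients, 300 per arm compared on medians is worth 300 × 0.47 = 141 at ρ = 0.3 and 300 × 0.63 = 189 at ρ = 0.8.

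**Where the loss comes from.** Dropping the adjustment alone leaves A/C = 0.73, 0.84, 0.94 and 0.98 at the four correlations. Using medians multiplies that by 2/π = 0.64. The scale adds little once baseline is in the model:
- Regressing log(1 + % change) on arm and log baseline gives exactly the treatment estimate of the adjusted log model, because only the baseline coefficient changes (by 1).
- In a simulation with lognormal values and coefficients of variation of 0.1 to 0.4, % change itself regressed on baseline lost only 0–10% at ρ of 0.5 or more.

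**Sensitivity.** With equal SDs, an unadjusted change score loses (1 − ρ)/2: 50% at ρ = 0, 35% at 0.3, 25% at 0.5, 15% at 0.7 and 5% at 0.9. In the same simulation, an unadjusted difference in medians lost 67–68% at ρ = 0, 50–55% at 0.5 and 39–42% at 0.9.

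**What this means for power at ρ = 0.3.** The standard error is √(π × 0.1985/300) = 0.0456 for medians and √(2 × 0.1456/300) = 0.0312 for the adjusted model.
- True log difference 0.10: 0.10/0.0456 − 1.96 = 0.23, power about 59%; adjusted model, 0.10/0.0312 − 1.96 = 1.25, about 89%.
- True log difference 0.20: 0.20/0.0456 − 1.96 = 2.43, about 99% even for medians.

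**The case against.** The strongest reply is that an outcome list names a summary, not a model. Nothing in the protocol says that the comparison is unadjusted or that it is a difference in medians, and the SAP may adjust for baseline and set the time points. This stands in part: it makes the loss conditional. It does not remove the point, because percent change is the measure that the protocol itself names and Section 6.3 says the arms are compared on it.

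A second reply is that Section 9.5 calls the safety analysis descriptive, in which case test efficiency matters little. That is a fair reading of one paragraph, but it conflicts with Section 6.3 and with the two-sided 5% level for secondary endpoints.

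A third is that the median resists outliers. So does the log scale for skewed values, and the median can stay as a description.

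A reader might infer more than the protocol supports:
- *That percent change as a scale is the fault.* The loss comes mainly from the missing adjustment and the use of medians.
- *That the baseline values are wasted.* Percent change uses them, though inefficiently.
- *That the repeated values are reduced to one change.* No time point is fixed, and percent change could be reported at every scheduled day.
- *That half the information is lost in any case.* About half applies to an unadjusted difference in medians; the loss for means is smaller at the assumed correlations.
- *That a toxicity difference would be missed.* Under the same assumptions, a log difference of 0.20 (about 22%) would still be detected with power of about 99% or more.

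**Conclusion.** The point holds in a limited form. The protocol contradicts itself on median against mean and on compared, tested or described, and those conflicts need no assumption to establish. It also states no baseline adjustment for its only continuous laboratory measure, although the baseline values exist.

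The size is conditional on an unadjusted comparison and on assumed SDs and correlations. Within the assumed range, the loss against a baseline-adjusted log model is about 37–53% for medians and about 4–34% for means; heavier-tailed data would narrow the gap for the median.

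The consequence is wider intervals, and exposure to chance baseline imbalance, in the second half of one secondary outcome. The proportions with grade III/IV events, the primary mortality analysis and the sample size are not affected.

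**What to change.** 1. Use one summary throughout: bring Section 6.3 into line with the Summary of Trial, Outcome Measures, Section 1.3 and Section 9.2. Keep median percent change as a descriptive column.
2. State in Section 9.5 whether the laboratory values are compared between arms or only described, and bring Section 6.3 and the two-sided 5% statement into agreement with that.
3. If they are compared, specify a model of the log follow-up value at the scheduled days (creatinine and electrolytes on days 3, 5, 7, 10, 12 and 14; haemoglobin and ALT on days 7 and 14), adjusted for the log baseline value and site. Report the ratio of geometric means with 95% CI, which still reads as a percent difference.

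The cost is a few sentences in Sections 6.3, 9.2 and 9.5, matching text in the SAP, and a little more analysis work. No new data, visits or patients are needed.

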### 9.3 SAMPLE SIZE

The current recommended treatment for HIV-associated CM are 7-14 day standard amphotericin B-based regimens . A non-inferiority design has been chosen as the primary aim of this trial is to identify an alternative safe and easy to administer short-course L-AmB treatment regimen that can be implemented in the settings where giving standard 7-14 day courses of amphotericin B deoxycholate-based treatment is difficult or impossible due to the need for daily intravenous infusions, close laboratory monitoring for the frequent drug induced toxicities, and intensive nursing and medical care. An efficacious single dose L-AmB treatment would also markedly facilitate CM therapy in settings

currently using standard courses of amphotericin B deoxycholate-based treatment, reducing the duration of hospitalisation and the associated risks (e.g. nosocomial sepsis) and costs. Ten-week mortality in our previous trials using amphotericin B deoxycholate-based regimens at the study sites has ranged from 28-41%, and is 30% with short-course high-dose L-AmB treatments in the recent phase-II study. We have therefore assumed a 35% 10-week mortality in both control and test groups. We want to show non-inferiority with a 10% margin (i.e. the upper margin of the one-sided 95% confidence interval of the difference in 10-week mortality between the two arms does not exceed 10%). The 10% margin has been chosen to ensure that only clinically unimportant differences are deemed non-inferior, and is in keeping with conventional practice. Using a one-sided  $\alpha = 0.05$  and 90% power, gives a sample size of 390 per arm (Figure 4). If the 10-week mortality is increased to 40% the equivalent sample size is 412 per arm. Making a conservative allowance for withdrawals and losses to follow-up of up to 8% (losses range from 2-4% in our trials), or a higher than anticipated mortality rate, we plan to enrol 425 patients per arm. Thus, we will randomise a total of **850 patients**. This will be the largest CM treatment trial conducted in Africa.

It is plausible that the intervention arm will lead to a greater reduction in mortality than the control arm through reduced toxicity or through another mechanism. In order to allow for this possibility, we have chosen to include superiority of the intervention as a secondary endpoint of the trial.

#### 9.4 INTERIM MONITORING & ANALYSES

An IDMC Charter will be drawn up that describes the membership of the IDMC, relationships with other committees, terms of reference, and decision-making processes (with a description of stopping rules and/or guidelines, if any). One analysis will be done at the end of the trial. There will be no formal interim analyses. Regular data and safety monitoring will be done by the IDMC.

#### 9.5 ANALYSIS PLAN (BRIEF)

Statistical analyses will be detailed in the statistical analysis plan. Briefly:

Analyses populations: 1) Intention-to-treat (ITT) population: all randomised subjects with valid informed consent; 2) Per-protocol (PP) population: a subset of the ITT population - subjects with major protocol deviations will be excluded from this PP population. 3) Safety population - a subset of the ITT population, consisting of all randomised subjects who receive at least one dose of study drug. 4) Pharmacokinetic (PK) population - a subset of the ITT population, consisting of all randomised subjects who receive at least one dose of study drug and have a PK profile. Primary analyses of efficacy will be based on the ITT population.

The primary endpoint analysis: The primary analysis will compare the treatment groups in terms of the proportion of participants who have died from any cause within 10 weeks. A generalised linear model (GLM) will be used. In this model, treatment group will be the sole predictor, using an identity-link function and binomial distribution to calculate an estimate for the (unadjusted) risk difference the treatment groups. If the upper limit of the one-sided 95% confidence interval (CI) for the risk difference falls below the non-inferiority margin of 10%, non-inferiority will be declared.

#### Secondary analyses.

We will conduct further analyses of the primary endpoint and analyse the secondary endpoints. These analyses will be done using a 5% two-sided significance level (i.e. to test for superiority).

Analyses of survival data will be conducted using unadjusted Cox regression analysis to calculate the hazard ratio (HR) and 95% CI between the treatment groups. Kaplan-Meier survival curves, and

survival percentages at 2, 4 and 10 weeks, will also be calculated by treatment group and overall. A log-rank test will be done to compare the survival curves between the treatment groups.

Proportions will be analysed using GLMs with treatment group as the sole predictor. The point estimate of the treatment effect with two-sided 95% CI will be derived.

For the analyses of cryptococcal clearance rates, we will perform linear regression of  $\log_{10}$  CFU against time for each patient. The means rates of decrease in  $\log_{10}$  CFU/ml/day will be compared between the two groups. We will calculate the difference in means together with the 95% CI. Rates of CFU decline will also be modelled using General Estimating Equations (GEE) methods.

Sensitivity analyses of the primary endpoint making different assumptions for the losses to follow-up will be conducted. Covariate-adjusted analyses for the primary endpoint will be conducted by adding pre-specified covariates into the GLM model to derive the adjusted risk difference and the upper limit of one-sided 95% CI. Imputation for baseline missing covariates will be made for the covariate-adjusted analysis.

**Stratified analyses:** Analyses stratified by ART status and other pre-defined baseline variables, such as clinical stage, will be performed. The other baseline variables will be defined in the analytical plan.

A full definition and explanation of all primary, secondary and stratified statistical analyses will be included in the statistical analysis plan.

**PK-PD analysis:** Plasma samples will be collected to describe the PK of liposomal amphotericin B, and enable the PK-PD of L-AmB for CM and the impact of PK variability on outcome to be determined. The serum PK of fluconazole will also be described. A portion of the CSF sample obtained for quantitative counts will be reserved to measure fluconazole concentrations, and thereby estimate the extent of penetration of fluconazole into the CSF. We will not attempt to measure concentrations of amphotericin B in CSF, as the drug is concentrated in the meninges and cannot be reliably detected in CSF. The PK-PD data will be modelled using a population methodology, using the program Pmetrics.

**Safety:** The safety analysis will be descriptive and the frequency and proportions of patients suffering clinical and laboratory-defined side effects (DAIDS grade III/IV adverse events) will be generated by treatment arms.

**Economic analysis:** An economic analysis will be conducted to provide evidence for the cost-effectiveness of short-course L-AmB treatment. The objective of the economic analysis is to estimate the cost consequences and the cost-effectiveness of short-course L-AmB treatment, compared to current care. Both societal and healthcare perspectives are chosen, and health service patient costs including household costs, treatment cost and hospitalisations in both arms will be compared over the trial period in a probabilistic approach, using Monte Carlo bootstrapping methods in STATA, @Risk software, and TreeAge. In the country-specific cost-consequence analyses, the societal and health service costs will be compared, and used along with the trial-wide primary endpoint data to perform cost-effectiveness modeling using a decision-tree model for each country with historical data as comparison.

